## Abstract

**Background:**

The acquisition and development of infant gut microbiota can be influenced by numerous factors, of which early antibiotic treatment is an important one. However, studies on the effects of antibiotic treatment in early life on clinical outcomes and establishment and development of the gut microbiota of term infants are limited. Disturbed microbiota composition is hypothesized to be an underlying mechanism of an aberrant development of the immune system. This study aims to investigate the potential clinical and microbial consequences of empiric antibiotic use in early life.

**Methods/Design:**

450 term born infants, of whom 150 are exposed to antibiotic treatment in early life and 300 are not (control group), are included in this observational cohort study with a one-year follow-up. Clinical outcomes, including coughing, wheezing, fever >38 °C, runny nose, glue ear, rash, diarrhea and >3 crying hours a day, are recorded daily by parents and examined by previously defined doctor’s diagnosis. A blood sample is taken at closure to investigate the infant’s vaccination response and sensitization for food and inhalant allergens. Fecal samples are obtained at eight time points during the first year of life. Potential differences in microbial profiles of infants treated with antibiotics versus healthy controls will be determined by use of 16S-23S rRNA gene analysis (IS-pro). Microbiota composition will be described by means of abundance, diversity and (dis)similarity. Diversity is calculated using the Shannon index. Dissimilarities between samples are calculated as the cosine distance between each pair of samples and analyzed with principal coordinate analysis. Clinical variables and possible associations are assessed by appropriate statistics.

**Discussion:**

Both clinical quantitative and qualitative microbial effects of antibiotic treatment in early life may be demonstrated. These findings can be important, since there is evidence that manipulation of the infant microbiota by using pre- or probiotics can restore the ecological balance of the microbiota and may mitigate potential negative effects on the developing immune system, when use of antibiotics cannot be avoided.

**Trial registration:**

ClinicalTrials.gov NCT02536560. Registered 28 August 2015.

## Background

The fetal intestine is (virtually) sterile, however, from birth onwards, the infant intestine becomes colonized with a wide variety of microorganisms [1]. The interaction between the host and its microbiota contributes fundamentally to overall health [2, 3]. For example, the microbial ecosystem provides the host with valuable metabolic features, such as metabolism of otherwise indigestible carbohydrates, xenobiotic metabolism, and production of essential metabolites such as vitamin K [4, 5]. Furthermore, the colonizing microorganisms play a key role in driving post-natal maturation of the infant gut and development of the mucosal immune system [6–10].

Disturbance of the microbial colonization patterns early in life can lead to long-lasting host effects and eventually disease. Aberrancies in microbial colonization patterns or distortion of the microbial ecology early in life might predispose the infant to the development of immune-mediated diseases. The gut microbiota has been associated with T-helper 2 (Th2) type diseases like allergy, wheezing and asthma, and also with T-helper 1 (Th1) type diseases, like inflammatory bowel disease, diabetes and obesity [11–24]. Also in non-immune mediated diseases, like infantile colic or irritable bowel syndrome, the fecal microbiota composition was found to be different from healthy controls [25, 26].

A range of factors can influence the composition of the intestinal microbiota and its establishment, like mode of delivery, feeding mode, contact with parents, siblings, and nursing and/or hospital staff when appropriate [27–29]. Antibiotic treatment during the early postnatal period, that has become common in modern obstetric and neonatal practice [15], is one of the important factors that can influence maturation of the infant gut microbiota and thus increase the risk of disease [11, 24]. A systematic review in 2011 of longitudinal studies on the effects of infant antibiotic use showed a higher risk for subsequent development of wheezing and/or asthma [30]. Other studies have shown an association between infant antibiotic exposure and growth rate and development of adiposity [31–33].

Relatively few studies have determined the direct effects of antibiotics on the composition of gut microbiota and/or addressed the mechanisms underlying this association [13, 29, 34]. Initial studies were based on culture-dependent techniques, but altered intestinal microbiota in antibiotic treated infants could already be identified by these relatively limited techniques [35, 36]. In the last few years, the development of culture-independent (molecular) approaches for studying the intestinal microbiota composition has changed and advanced our original perspective and insight into the impact of the composition of the microbiome [37, 38]. By using molecular fingerprinting and determination of 16S rRNA genes (by quantitative polymerase chain reaction, qPCR), overgrowth of *Enterococci* and arrested growth of *Bifidobacterium* in infants exposed to antibiotics in the first week of life has been described [34].

Overall, evidence is growing that an aberrant microbiota composition as a result of antibiotic treatment can have clinical effects, but more robust studies are needed with a higher number of patients to elucidate the exact effects of antibiotics on the developing microbiota and its association with health in the first year of life. This study therefore aims to investigate the potential clinical and microbial consequences of empiric antibiotic use in early life by following a large cohort of 150 treated and 300 untreated infants and compare them with respect to their health status as well as their developing gut microbiota.

## Methods/Design

### Study design and population

A prospective, observational cohort study with a one-year follow-up is currently conducted to determine the clinical effects and impact on the gut microbiota composition of empiric antibiotic use in early life. Infants are recruited from the maternity wards and neonatal wards of four teaching hospitals in the Netherlands: the St. Antonius Hospital in Nieuwegein, the Tergooi Hospital in Blaricum, the Gelre Hospitals in Apeldoorn and the Meander Medical Center in Amersfoort. This study was approved by the joined Medical Ethics Committee (VCMO) of the St Antonius Hospital and Meander Medical Center (nowadays MEC-U: Medical Research Ethics Committees United (Nieuwegein)). In The Netherlands, since 2013 studies only need to be approved by one Ethics Committee. Subsequently, for other participating centers, proof of local feasibility needs to be given. The approved protocol was consequently checked for local feasibility and expertise at Tergooi Hospital and Gelre Hospitals and permission for study implementation was obtained by the respective boards of directors. The study is performed in accordance with the ethical standards laid down in the 1964 Declaration of Helsinki and its later amendments.

All parents of term infants (≥ 36 weeks of gestational age) who stay in the hospital for at least 24 h, are approached for participation in the study.

In total 150 infants, treated with antibiotics because of (a high suspicion of) a perinatal infection during the first week of life, will be recruited. The control group comprises 300 healthy newborns, born in the hospital and needing clinical observation for 24–48 h for several reasons like maternal comorbidity, low probability of neonatal infection, blood sugar monitoring, meconium containing amniotic fluid, or delivery by caesarean section. For a balanced composition of the control group, as much as possible infants that are suspected to have a neonatal infection but for whom watchful waiting is allowed (and no antibiotic treatment has to be started) will be included.

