### Statistical analysis

We will evaluate the potential relationships between antibiotic use in early life and the various (clinical) endpoints. Variables are verified for normal distribution and *t*-tests will be used for testing the null hypothesis. Either logistic regression analysis or cox regression analysis will be applied to the data (appearance of the primary endpoint(s) will be recorded as specifically as possible), so that odds ratios or hazard ratios and their 95 % confidence interval can be presented for description of the relationships. Multivariate models will be used to assess confounders and confounding effects. We will perform post hoc analyses to look for potential effects of the different antibiotic regimes. Outcomes may, possibly, be classified into subgroups. According to antibiotic treatment after the first two weeks, children will be grouped based on the number of antibiotic courses during the first year of life (0 / 1 / 2 or more courses). Within the ‘treatment groups’ a distinction can be made between the class or spectrum of the prescribed antibiotics.

Microbiota composition will be described by means of abundance, diversity and (dis)similarity. Diversity is calculated using the Shannon index [42] and differences in this index will be tested with Mann–Whitney *U* test. Dissimilarities between samples, or between-sample diversity, are calculated as the cosine distance between each pair of samples and analyzed with principal coordinate analysis (PCoA). All statistical analysis will be conducted using SPSS version 22.0 (SPSS Inc., Chicago, IL, USA) and the vegan software package in R (Foundation for Statistical Computing, Vienna, Austria).

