The fact that children who are sick and receive antibiotic treatment may differ from healthy children, who do not need antibiotic treatment at birth, is one of the most important limitations of this study. However, to our opinion, there are no opportunities to bypass this problem, as ethical concerns prevent us from performing a double blind randomized controlled trial. Another limitation of this study may be the fact that bacterial composition may change as a consequence of freezing fecal samples. For example, levels of *Bacteroidetes* have been shown to be reduced in frozen samples [3, 50, 51]. As all samples will be obtained by the parents and stored in their home freezers, no information on potential differences in storage conditions between samples can be obtained. We try to minimize this variation by instructing (by one of the investigators) all parents on how to collect the faecal samples, which makes the collection procedure as standardized as possible. We do realize that studying the microbiota composition of fecal samples may not be the best method to assess the general composition and the effect of antibiotics in the gastrointestinal tract. Stool samples therefore are used as a proxy for the study of the gut microbiota as these samples are easier to collect than biopsy samples and avoid invasive procedures (and associated ethical issues). A limitation of sampling the gut microbiota is that once the sample is taken, alterations in the relative proportions of various bacterial species can occur so that the sample might no longer accurately reflect the composition of the microbiota in vivo by the time it is processed [3]. This is a well-known problem with respect to molecular approach of microbiota composition and to date it is impossible to collect biopsy samples from infants (and healthy volunteers generally) on a large scale due to the practical and ethical challenges indicated above [3].

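### The antibiotic group mixes infants with an actual perinatal infection and infants treated only on suspicion, and no planned analysis separates them, so the antibiotic contrast may be confounded by infection

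*Protocol article*

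**What the plan says.** The Background section gives the aim: "This study therefore aims to investigate the potential clinical and microbial consequences of empiric antibiotic use in early life". The Study design and population section repeats it.

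The same section then defines the two groups:
- **Exposed:** "In total 150 infants, treated with antibiotics because of (a high suspicion of) a perinatal infection during the first week of life, will be recruited". Through the words in parentheses, both actual infection and strong suspicion are eligible.
- **Controls:** "The control group comprises 300 healthy newborns, born in the hospital and needing clinical observation for 24–48 h for several reasons". Among them the investigators want as many as they can get of "infants that are suspected to have a neonatal infection but for whom watchful waiting is allowed", but no number is fixed.

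The exclusion criteria remove only those perinatal infections that are severe enough to need transfer to intensive care. Less severe actual infections stay eligible.

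The Statistical analysis section plans adjustment: "Multivariate models will be used to assess confounders and confounding effects". On treatment it says: "We will perform post hoc analyses to look for potential effects of the different antibiotic regimes". It also groups children by the number of later antibiotic courses, allows a split by class or spectrum of drug, and mentions possible outcome subgroups without naming a variable. None of these is by infection status.

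The Discussion counts this among the study's main limitations: "The fact that children who are sick and receive antibiotic treatment may differ from healthy children". It says that the problem cannot be avoided, because a randomised trial would be unethical.

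**The concern.** In an infant with an actual infection, illness and antibiotic arrive together, and the healthy controls offer no comparison that pulls them apart. In an infant treated on suspicion and never confirmed, infection is a much weaker rival explanation. Pooling the two means that a difference in eczema, in other clinical endpoints or in the microbiota could arise partly from infection, and the reader could not tell.

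The stake is attribution. The Discussion looks ahead to interventions that limit the harm of early antibiotic exposure. That step needs the effect to belong to the antibiotic rather than to the illness that prompted it.

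**Working it through.** **Inputs from the Power calculation section.** Eczema 20% in controls and 35% in treated infants; 150 treated and 300 controls; 15% dropout; power 80%; alpha 5% (taken as two-sided). Evaluable infants: 150 × 0.85 = 127.5 treated and 300 × 0.85 = 255 controls.

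**Assumed, because the article gives neither:** the share *f* of treated infants with confirmed infection, and the increase *e* in eczema risk caused by infection itself.

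**1. The plan's own figure.** A two-sided two-proportion test at 80% power with 1:2 allocation needs 101 + 202 = 303 evaluable infants, or 357 after 15% dropout (393 with continuity correction). The stated 450 is not reproduced. It is larger than needed, which is a separate and conservative discrepancy and no evidence for this point. It does leave room for a restricted contrast.

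**2. Power with all treated infants.** With pooled rate p̄, s0 = √[p̄(1−p̄)(1/n1+1/n2)] and s1 = √[p1(1−p1)/n1 + p2(1−p2)/n2], power = Φ[(p1−p2−1.96·s0)/s1].
- p̄ = (127.5×0.35 + 255×0.20)/382.5 = 0.25
- s0 = 0.0470, s1 = 0.0491
- Power = Φ[(0.15 − 1.96×0.0470)/0.0491] = Φ(1.18) = 88.1%

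**3. False-positive rate if antibiotics do nothing.** Suppose unconfirmed infants have the control rate of 20%. The treated rate is then 20% + *f*·*e*, and the spurious difference is *f*·*e*. The two-sided rejection rate adds both tails, from the same formula. The result depends only on the product *f*·*e*.

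| Confirmed share *f* | *e* = 5 points | *e* = 10 points | *e* = 15 points |
|---|---|---|---|
| 5% | 0.25 points; 5.1% | 0.5; 5.2% | 0.75; 5.4% |
| 10% | 0.5; 5.2% | 1.0; 5.7% | 1.5; 6.6% |
| 20% | 1.0; 5.7% | 2.0; 7.7% | 3.0; 10.9% |
| 30% | 1.5; 6.6% | 3.0; 10.9% | 4.5; 17.8% |
| 40% | 2.0; 7.7% | 4.0; 15.2% | 6.0; 27.3% |

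The 15-point column borrows the size of the plan's hypothesised antibiotic difference (35% − 20%) and gives it to infection. It is an illustration, not an estimate. The calculation is unadjusted.

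**4. Power of a contrast limited to unconfirmed treated infants** (20% versus 35%, all 255 controls kept):

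| Confirmed share | Treated infants left | Power |
|---|---|---|
| 10% | 114.75 | 85.9% |
| 20% | 102 | 83.2% |
| 30% | 89.25 | 79.9% |
| 40% | 76.5 | 75.7% |

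These figures do not depend on *e*. They assume that the planned 15-point difference holds in the unconfirmed infants.

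**5. What the planned safeguards can do.**
- The intensive-care exclusion removes the most severe infections only.
- Suspected-but-untreated controls are a counterpart for infants treated on suspicion, not for infants with actual infection, and their number is open.
- Multivariate models need overlap. Confirmed infection has essentially no counterpart among healthy controls, so adjustment has little to work with.
- Splits by regime, number of courses, class or spectrum do not identify infection.

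**The case against.** The case on the other side has real weight.

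- **A reader might infer that pooling contradicts the aim of studying empiric use.** It does not. Empiric describes how treatment starts, before confirmation. An infant later found infected may also have started empirically.
- **A reader might infer that an infection effect will be reported as an antibiotic effect.** The documents do not show this. They give no confirmed share and no infection effect, and at the low end of the table the distortion is negligible (0.25 points; 5.1% against 5%).
- **A reader might count a longer or different treatment course in infected infants as further infection bias.** A different course is antibiotic exposure, and post hoc analyses by regime are planned.
- **The plan is not blind to the problem.** It seeks suspected-but-untreated controls, plans adjustment and states the limitation openly.
- **Limiting the exposed group has its own flaw.** Confirmation is known only after treatment starts and has no parallel in controls. The difference between infants under strong suspicion and newborns observed for other reasons remains.
- **A further sensitivity analysis could sit in a full protocol or analysis plan that is not shown.**

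The first five stand. They rule out calling this a contradiction or a proven bias, and they argue against replacing the main contrast. The last stands in part. The article itself fixes the exposed group, names its splits and declares the problem unavoidable, so the point can fairly be raised on what it states.

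**Conclusion.** The point holds as a possible confounding that the plan leaves open, not as an established bias. The exposed group mixes actual and suspected infection, and no named analysis separates them. The listed safeguards do not reach the infants with actual infection. The Discussion's statement that nothing can be done is too strong: it is argued from the impossibility of randomising, whereas separating infants by infection status within the treated group needs no randomisation and removes part of the problem.

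The size is unknown. Under the assumed shares (5% to 40%) and infection effects (5 to 15 points), the two-sided false-positive rate lies between about 5% and 27%. This rests on no antibiotic effect, a 20% rate in unconfirmed infants and an unadjusted test. A supporting contrast without confirmed cases keeps about 80% power for confirmed shares up to about 30%. This is a cheap improvement.

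**What to change.** - **Classify.** Before outcome data are seen, label each treated infant from the hospital record as infection confirmed or not confirmed. The article says that delivery and hospital data are extracted; that this covers cultures and discharge diagnosis is an assumption to check.
- **Analyse.** Keep all treated infants versus controls. Pre-specify unconfirmed treated infants versus controls as a key supporting contrast for eczema, the other clinical endpoints and the microbiota. Where numbers allow, also compare them with the suspected-but-untreated controls.
- **Interpret.** Attribute an effect to antibiotics rather than infection only if the supporting contrast agrees with the all-treated contrast. State that the supporting contrast selects on information that arises after treatment starts, and that it does not remove the remaining difference between infants under high suspicion and healthy controls.
- **Discussion.** Replace the claim that the problem cannot be avoided with a statement that it can be reduced in part.

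The cost is one more variable to extract, a paragraph of analysis text, and lower power in the supporting contrast (88% falling to 86/83/80/76% at confirmed shares of 10/20/30/40%). Power against the suspected-but-untreated controls alone cannot be given, because their number is not fixed. Recruitment and treatment do not change.

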### Inclusion and exclusion criteria

Inclusion criteriaTerm-born babies (≥ 36 weeks gestational age)(Short) stay on maternal ward or admission to neonatal ward because of antibiotic treatmentSigned informed consent by the parents

Exclusion criteriaCongenital illness or malformationsSevere perinatal infections for which transfer to the neonatal intensive care unit is neededMaternal probiotic use ≤ six weeks before deliveryInsufficient knowledge of the Dutch language.

Infants suspected of neonatal infection will be treated with antibiotics according to the local hospital protocols. All hospitals use gentamycin in combination with either penicillin, amoxicillin or amoxicillin/clavulanic acid. During the study period, type of feeding is closely monitored, as parents monthly report the type of feeding on the calendar list (breast- or formula feeding). Parents are free in their choice of feeding regime, and after six months infants will be on solid food, but not all the infants in the study will have the exact same diet as this is neither feasible nor ethical. Mother’s intake of antibiotics or drugs during pregnancy, delivery and during breastfeeding (if applicable) will be recorded. Delivery/hospital data will be extracted from patient records.

All parents have to give informed consent prior to inclusion in the study. Follow up continues during the first year of life, in which parents collect and store eight fecal samples of their infant. Parents are also asked to collect a fecal sample of their child around the 2^nd^ birthday and they give permission for a possible approach for a follow-up in about 5–6 years.

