### Outcomes

#### Symptoms via calendar checklist

Parents are instructed to record a (for this study) designed daily checklist of clinical symptoms, which include coughing, wheezing, fever >38 °C, runny nose, glue ear, rash, diarrhea, >3 h of crying within one day (24 h). Table 1 shows the various symptoms, which should be recorded by the parents. Descriptions standardize the way of recording as much as possible. The checklists are designed as a calendar and parents are requested to return a list (at the end of) every month. As a motivation for returning the list, we send back a contemporary Dutch magazine for young parents, monthly, after receiving their list.

**Table 1 Tab1:** Description of symptoms

Coughing	Your infant coughs several times a day and/or has coughing. Regularly there are signs of cold. Don’t record cough because of choking.
Wheezing	During expiration you notice a whistling, wheezy sound coming from the lower airways. During expiration your child is trying to squeeze the air outwards. Don’t record wheezing coming from or through the nose.
Fever >38 °C	Clear from itself, whereby it is important you use a rectal thermometer, measure twice and the temperature is >38 °C on both occasions.
Runny nose	Signs of cold with white/yellow/green mucus running from the nose;
Glue ear	Your child seems to have earache and/or grasps its ear (the ear frequently is high-colored or bends) and/or glue egresses from the ear.
Rash	More than one day existing skin-redness (spots, rash, pimples) on the face, arms or legs, trunk. Disease-symptoms are not necessarily present. The rash can be eczema; eczema mostly is red, moistly, scaly and may itch. Infants cheeks are affected mostly. When children grow up, elbow and knees are preferred sites.
Diarrhea	Increase in stool frequency to twice the usual number per day, that continues more than one day. The content may be watery or mucous.
>3 crying hours a day	Clear from itself, whereby the total crying episodes add up to more than three hours a day (24 h) in total.

At baseline, parents have to fill out an online questionnaire containing questions on demographics, comorbidity and use of medication. This questionnaire includes: gestational age and birthweight of the child, maternal comorbidity (medication during pregnancy and delivery), environmental factors (habitat, housing), parental smoking habits, siblings, pets, chronic diseases and hereditary diseases, ethnicity, education.

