## Discussion

To the best of our knowledge, this is the first prospective observational cohort study, with a follow-up of one year, addressing clinical outcomes after empiric antibiotic treatment in early life which at the same time investigates the development of intestinal microbiota composition after this antibiotic exposure. Subsequently, extensive clinical outcomes can be linked to microbiota composition over time. This study includes a total of 450 infants, of whom 150 are exposed to antibiotic treatment shortly after birth and 300 controls. Previous studies addressing consequences of antibiotic treatment in early life were hampered by a retrospective approach [11, 33, 39, 47], divergent study populations [48], smaller sample sizes [17] or a limited period of follow-up [34, 49].

By assessing an extended number of clinical parameters in a fairly large group, and subsequently strictly selected homogeneous subgroups of infants, bias due to confounding factors such as mode of delivery and type of feeding is expected to be reduced. Results from this study may improve our understanding of the evolving microbiota in term infants. Also, by collecting fecal samples at eight time points during the first year of life and around the second birthday, long-term microbiota development can be investigated.

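### The cohort starts at 36 weeks but is labelled term, and the planned microbiota comparison takes no account of gestational age although it is recorded

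*Protocol article*

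**What the plan says.** **Population.** Study design and population, and Inclusion and exclusion criteria, both describe the infants as term and both set the lower limit at "36 weeks gestational age". The abstract's Methods/Design paragraph speaks of "450 term born infants, of whom 150 are exposed to antibiotic treatment in early life" without repeating the limit. The Discussion concludes that "Results from this study may improve our understanding of the evolving microbiota in term infants".

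**Data.** Under Symptoms via calendar checklist, the baseline questionnaire is described thus: "This questionnaire includes: gestational age and birthweight of the child". Gestational age is therefore available for analysis.

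**Microbiota analysis.** The Aims section puts the treated-versus-control microbiota comparison first and introduces clinical outcomes second. Statistical analysis gives the Shannon index as the diversity measure and says that "differences in this index will be tested with Mann–Whitney" U test. Between-sample dissimilarity is measured by cosine distance and explored by principal coordinate analysis (PCoA). No covariate is mentioned for either.

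**Confounding.** The same section plans multivariate models to examine confounders, without listing covariates. That sentence stands in the paragraph on the clinical endpoints, next to the odds ratios and hazard ratios. The Discussion gives delivery mode and feeding as examples of confounders, and concedes that treated and healthy infants may differ.

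**The concern.** Two things do not fit together. First, infants of 36 weeks and 0 to 6 days are late preterm in ordinary usage, so a result worded for term infants would rest partly on infants whom most readers would not count as term. (The 37-week convention is general knowledge; the article does not state it.)

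Second, the groups form by different routes. Infants are treated on suspicion of perinatal infection. Controls are observed for reasons such as maternal comorbidity, blood sugar monitoring, meconium-stained fluid or caesarean delivery. Nothing matches the groups on gestational age. Immaturity could influence both early treatment and gut colonisation, and a two-sample rank test cannot separate the two. Part of a difference credited to antibiotics could then be a difference in gestational age.

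**Working it through.** The plan gives no figure on this point to reproduce: no gestational-age distribution and no expected microbiota effect. The check is therefore a sensitivity calculation with declared assumptions.

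**Inputs from the article (Power calculation).** 150 treated and 300 controls, with 15% dropout. Evaluable: 150 × 0.85 = 127.5, taken as 127, and 300 × 0.85 = 255. Applying this dropout, which was set for the eczema endpoint, to the stool samples is itself an assumption.

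**Assumed inputs (no source in the article).**
- Δp: share of 36-week infants among treated minus share among controls, 0 to 10 percentage points (controls 5%; treated 5%, 10% or 15%).
- d: difference in Shannon diversity between 36-week and older infants, 0.3 to 1.0 SD.
- Antibiotics have no effect; the test is two-sided at 5%; the rank test has efficiency 0.955 relative to the t-test.

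**Formulas.**
- Shift in the group contrast = Δp × d.
- SE = √(1/127 + 1/255) = √(0.007874 + 0.003922) = 0.1086 SD.
- z = (shift / SE) × √0.955.
- Rejection probability = 1 − Φ(1.96 − z) + Φ(−1.96 − z).

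**Example.** Δp = 0.10 and d = 1.0 give a shift of 0.10 SD and z = (0.10 / 0.1086) × 0.977 = 0.90. The rejection probability is 1 − Φ(1.06) + Φ(−2.86) = 14.7%.

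| Share at 36 weeks, treated vs control | d = 0.3 | d = 0.5 | d = 0.8 | d = 1.0 |
|---|---|---|---|---|
| 5% vs 5% | 5.0% | 5.0% | 5.0% | 5.0% |
| 10% vs 5% | 5.2% | 5.6% | 6.5% | 7.3% |
| 15% vs 5% | 5.8% | 7.3% | 11.1% | 14.7% |

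A still wider gap, 20% vs 5% with d = 0.8, shifts the contrast by 0.15 × 0.8 = 0.12 SD and gives 19.1%.

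**Reading.** With no imbalance there is no bias. At 5 points the error rate stays between 5.2% and 7.3%. It reaches about 15% only when a threefold difference in share meets a full 1 SD effect. Even then the shift, 0.10 SD, is smaller than one standard error. If the imbalance runs the other way, so does the shift, and a real difference could be masked or exaggerated.

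**The case against.** The case on the other side is substantial.

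- **The limit is disclosed.** Both eligibility statements print the 36-week limit beside the word term, so it can be read as the study's own definition. A reader might infer that the article contradicts itself or enrols a different population from the one it names. It does neither: the limit is consistent, and in the assumed examples in the table at least 85% of each group is at 37 weeks or more. What stands is that the abstract and discussion use the word without the limit, and it will be understood in its usual sense.
- **Imbalance is not shown.** A reader might infer that 36-week infants are likely to be unevenly spread. The article does not support that. Blood sugar monitoring could bring such infants into the control group, and the plan seeks controls with suspected infection managed by watchful waiting. Both could offset a higher share among the treated. Only that the groups may differ can be said.
- **Gestational age is not ignored by the study as a whole.** It is collected, confounder models are planned, and a condensed article may leave the covariate list to a fuller plan. This stands for the clinical outcomes. It answers less for the microbiota, where the article names a test that has no place for a covariate.
- **Other covariates have the same claim.** Delivery mode and feeding matter at least as much on the article's own account. This stands, and is why the adjustment should not be for gestational age alone.

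**Conclusion.** The point holds in a limited form, as a minor improvement. On the face of the text, the label term is attached to a 36-week limit, and the microbiota methods named for a non-randomised comparison are unadjusted although a relevant baseline variable is recorded. The size of any resulting bias is unknown. The range of 5% to roughly 15% for the false-positive rate depends wholly on the assumed shares and effect sizes, and the lower end is as compatible with the article as the upper. It does not follow that the comparison is biased, or in which direction. The clinical analyses are not affected by this criticism.

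**What to change.** 1. Describe the cohort as infants of 36 weeks or more, in the abstract and discussion as well as in the eligibility section.
2. Report gestational age by group, including the share at 36 weeks.
3. Keep the Mann–Whitney test and PCoA, and supplement them with a regression model of Shannon diversity and a covariate-adjusted distance-based analysis of the cosine distances. Both should include gestational age in weeks with the other recorded confounders, such as delivery mode and feeding.
4. Repeat the lead treated-versus-control comparisons in infants of at least 37 weeks as a sensitivity analysis, and base statements about term infants in the usual sense on it.

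**Cost.** No new data and no change to enrolment; some extra analysis and a few words. The restricted set loses a little precision. With 15% vs 5% at 36 weeks, 127 × 0.85 ≈ 108 and 255 × 0.95 ≈ 242 infants remain. The SE becomes √(1/108 + 1/242) = 0.1157 against 0.1086, about 7% larger.
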